### 5.3 Additional measures

At baseline, we measure the optimism with the Life-orientation Test (LOT-R, (Glaesmer et al., 2008)). After completion of treatment, acupuncture therapists will be asked to guess which interventions patients received and their confidence with this guess. This will allow checking whether treatment providers were successfully blinded to briefing assignments. Patients will be also asked to guess which briefing interventions they received. The patient guesses will be obtained after disclosure of the study aim at the end of the treatment.

In addition we measure the empathy of the physician who performs the briefing, using the German Version of the "Consultation and Relational Empathy" (CARE) instrument (Neumann et al., 2008).

### 5.4 Safety Outcomes

The primary safety measure is the patient report regarding SAEs which will be documented in the SAE report form. Furthermore we will assess acupuncture side effects, which are defined as a primary outcome (please see above).

## STUDY DESIGN AND COURSE OF STUDY

### 6.1 General Study Design and Justification of the Design

We will perform a randomized double-blind four-armed trial with a 2 x 2 factorial design with two independent factors (effectiveness briefing and side effect briefing). All patients will have a four-week acupuncture treatment (8 sessions) and receive a follow up questionnaire after 6 months. Before the first acupuncture session (ca. 30 minutes) and before the second acupuncture session (ca. 15 minutes), there will be a consultation with the physician in which the briefing interventions will take place. We aim to recruit a total of 150 patients.

We will use central block-randomization with variable block length in a 1:1:1:1 ratio.

We will test the following null hypotheses:

Research question on effectiveness:

(1a) high expectation briefing = regular expectation briefing for change in expectation

(1b) high expectation briefing = regular expectation briefing for change in back pain

a priori ordered hierarchical test procedure will be used

Research question on side effects:

(2) high side effect briefing = regular side effect briefing for amount of side effects reported.

### 6.2 Methods of Minimizing Bias

To reduce bias, we randomize the patients to the intervention. Patients in the study will not be aware that briefing is the study intervention and they will be blinded to the briefing group application. The allocation is concealed by using the software secuTrial®. We will furthermore ask the patients to provide a post-treatment guess to measure whether blinding patients was successful. The acupuncturists will be blinded and we will ask them for a post-treatment guess as well.

### **6.2.1 Randomization**

We will use central block-randomization with variable block length in a 1:1:1:1 ratio. Randomization sequence will be stratified by sex using R (Version 3.1.0) by a statistician not further involved in the study. For allocation of patients via the internet the software secuTrial® (Clinical Trial Center, University Hospital Zurich) will be used (see Appendix).

### **6.2.2 Blinding Procedures**

We will perform a randomized double-blind design: patients, and acupuncture therapists will be blinded to patient group assignment. The PhD students will screen patients for study inclusion and obtain informed consent. A medical doctor not involved in the acupuncture treatment will receive the randomization assignment for the patient and carry out the briefing interventions. The acupuncture therapists do not have any information about the allocation of patients. The patients do not have any information about the study aim and will be asked for a retrospective consent after the end of the study. Thus, it is not expected that participants know about any expectancy and side effect manipulation and hence will not realize the difference between study intervention and control intervention.

Towards the public we have to blind the study aim and therefore communicate the study aim as agreed with the SNF Forschungsrat: “we aim to develop an instrument for assessing patient’s expectations, implement it practically and test the influence of expectations on treatment outcome.”

## **6.3 Unblinding Procedures (Code break)**

Not intended because all patients receive the same medical treatment.

# **7 STUDY POPULATION**

## **7.1 Eligibility Criteria**

### **7.1.1 Inclusion Criteria**

Male and female patients aged 18 to 65 years with chronic non-specific low back pain (CLBP) according to Deyo et al. (2014) with an average pain severity of at least 4 on a 0-10 numeric rating scale and at least half of the days per months with pain in the last 6 months will be eligible for this study.

### **7.1.2 Exclusion Criteria**

Patients will be excluded if they had have acupuncture treatment within the last 12 months; are breast-feeding or are known pregnant, have a known blood coagulation disorder or take of coagulation inhibiting drugs with the exception of aspirin. Furthermore they are excluded in case of their CLBP being caused by a known malignant disease, trauma, the presence of a known rheumatic or autoimmune disorder, a history or planned surgery of the spinal column of the low back in the next 6 months, regular intake of analgesics (> once per week) because of additional disease, intake of centrally-acting analgesics, regular intake of corticosteroids or injections with corticosteroids within the last 8 weeks before randomization (specified in a studyspecific SOP),

or a history of severe acute or chronic disorders that do not allow participation in the therapy. Further exclusion criteria include known alcohol or substance abuse, insufficient German language skills, current application for a pension claim.

## **7.2 Recruitment and Screening**

Patients will be recruited via family physicians from a research network. This research network is managed by the Institute of Family Medicine of the University Zurich and includes 200 physicians that are used to contribute to research. The family physician research network is currently not involved in any other research projects on CLBP that may interfere with the recruitment for this trial. Furthermore, the Horten Center at the University Zurich hosts a comprehensive register of low back pain patients and will inform about the study. In addition to these recruitment strategies, patients will be recruited via local newspapers, patient organizations, and via the website of the Institute for Complementary and Integrative Medicine. The recruitment of about 150 patients with CLBP during a period of 18 months seems well feasible. For recruitment, residents who perform under the supervision of [name] will be asked to inform their chronic low back pain patients in the outpatient clinics about the possibility to take part in our study. For ensuring strong and reliable support, we will build up a close network to those doctors.

As a second recruitment strategy, we will contact company doctors through the Swiss association of occupational medicine and ask them for their assistance in making our study public to their patients.

Patients will not be financially compensated for their participation.

## **7.3 Assignment to Study Groups**

Randomization will be conducted by the doctor who includes the patients into the study using the software secuTrial® (Clinical Trials Center Zurich), to ensure allocation concealment (see Appendix).

## **7.4 Criteria for Withdrawal/ Discontinuation of Participants**

Participants have the right to abort the study at any time and without providing a reason. The study coordinator has the right to exclude participants if they provide wrong information or do not follow the safety guidelines.

# **8 STUDY INTERVENTION**

## **8.1 General Information**

### **Study interventions (briefing intervention)**

Group 1: High expectation briefing + regular briefing about side effects (no additional briefing)

Group 2: High expectation briefing + intense briefing about side effects (additional briefing)

Group 3: Regular expectation briefing + regular briefing about side effects (no additional briefing)

Group 4: Regular expectation briefing + intense briefing about side effects (additional briefing)

### **Procedure:**

Independent of the briefing intervention all patients will receive the patient information leaflet about the study with common information about possible side effects as part of the informed consent procedure at the first visit. We transferred the basic safety profile from a study observing over 2 million acupuncture treatments into a patient information leaflet that is available for routine clinical care (Witt et al., 2009).

The briefing interventions will be provided through in-person contact with the doctor and also include written materials for the patients to take home before the first treatment session. The written materials have been adapted to the four groups. The initial effectiveness briefing will have a duration of about 20 minutes; the initial safety briefing will have a duration of 10 minutes. A manual for the briefing interventions has been developed and the medical doctors providing the briefing intervention will be trained in the briefing intervention as well as in communication skills (empathic style).

Patients will have a face-to-face booster visit according to their group allocation at the second treatment session, which will take around 15 minutes (10 minutes effectiveness briefing and 5 minutes safety briefing).

As a second booster, patients will receive emails or letters including a reminder of their appointments, more information about acupuncture for chronic low back pain as well as possible side effects according to their group allocation after the third and sixth acupuncture session.

### **Medical treatment**

All patients will receive a standardized acupuncture. Acupuncture has been used successfully before in trials applying verbal suggestion as an intervention, and has been shown to be superior to conventional standard care (Haake et al., 2007). All patients will receive the same penetrating acupuncture that is provided at no acupuncture points (6 predefined points bilateral). It has been developed in a consensus procedure for our previous trial and resulted in a 50% pain severity reduction in 38% of the patients (Brinkhaus et al., 2003; Brinkhaus et al., 2006). Patients in this trial will receive 8 sessions (two per week) over four weeks, because one of our recent trials found > 25mm pain reduction on a VAS after 8 treatments (Pach et al., 2013) and most trials in our patient level meta analyses provided between 6 and 10 treatments (MacPherson et al., 2013). Needles (B type needles, CE-certified, sterile and in single use, size No.8 (0.30) x 30mm, produced by medical Seirin Corporation, Shizuoka, Japan) will be left in for 25 minutes and will be manually stimulated twice (beginning and end of the treatment sessions). Stimulation will be standardized.

According to the communication and the request by the SNF Forschungsrat, we will call this type of medical treatment acupuncture or scientific effective acupuncture, in German „wissenschaftlich wirksame Akupunktur“.

The first acupuncture treatment will be delivered after the briefing by two therapists (PhD students) that will be especially trained for this type of acupuncture. Previous experience shows that this type of standardized acupuncture is easy to learn and to apply. Acupuncture training will include video documentation, extensive hands on training and supervision by a medical doctor with experience in this type of acupuncture. The patient-therapist interaction will be standardized and performed in the same treatment rooms for all patients. We have developed a manual for the communication style and will train the acupuncture therapists. The therapists will be especially trained to perform this standardized patient-doctor interaction in order to limit

biases due to this interaction. Therapists will document the adherence to the acupuncture treatment and to the standardized patient-doctor interaction after each session. All deviations from the study protocol will be documented. Since the therapists have to deliver the same treatment for all experimental conditions the study team is very optimistic about delivering a highly standardized treatment. Supervision will be provided by the principal investigator.

### **8.1.1 Study Intervention**

#### **Study Intervention A) Effectiveness**

Briefing intervention: high expectation

#### **Study Intervention B) Side Effects**

Briefing intervention: intense briefing about side effect

### **8.1.2 Control Intervention**

#### **Control Intervention A) Effectiveness**

Briefing intervention: regular expectation

#### **Control Intervention B) Side Effects**

Briefing intervention: regular briefing about side effects

## **8.2 Administration of Study Intervention and Control Intervention**

### **8.2.1 Study Intervention A) Effectiveness**

The *high expectation briefing* will emphasize the large overall effects of acupuncture, which have been demonstrated in many studies, and highlight that acupuncture has been shown to be superior to conventional standard care. Patients will be told that, since acupuncture requires extensive training, the acupuncture therapists have received special training and are under close supervision of other team members so that they can provide a very high quality treatment. Patients will also receive the information that our team was very successful in using acupuncture to treat similar patients with CLBP, and we have shown the effectiveness of acupuncture in large clinical trials. Finally, patients will be informed that most patients are very satisfied with acupuncture treatment and would recommend it to other patients.

The booster visit at the second acupuncture session will begin with a short assessment of patients' experience of the first acupuncture session and any change in symptoms. In case of worsening or no change the patient will receive the information that this is a quite common experience of many patients and that the acupuncture effect will usually start after the second treatment and will increase over time. In case of improvement of health status the patient will receive the information that this initial response can be regarded as a positive sign for a strong ongoing response to acupuncture treatment. In both clinical situations, the effectiveness of acupuncture in treating patients with CLBP will be repeated again. In the written information, patients will be informed again about the effectiveness of acupuncture and encouraged to remember situations in which they can move well despite problems of pain. They will be encouraged to list on the sheet situations with reduced or without pain. Problem talk will be avoided and positive language about change in symptoms, pain perception, and optimism will be used.

### **8.2.2 Study Intervention B) Side Effects**

The goal of the *intense safety briefing* is to provide information sensitizing patients to the presence of side effects during acupuncture treatment. The doctor will explain in detail the side effects that have been observed in a large study with over 2 million acupuncture treatments. Patients will receive the patient information leaflet that was developed based on this study and the doctor will advise them to read it carefully because he would like to discuss any questions they may have during the next visit. During the booster sessions the medical doctor will ask if side effects have occurred, explain the possible side effects again, and ask the patients if they have any questions about side effects.

### **8.2.3 Control Intervention A) Effectiveness**

The *regular expectation briefing* it will be mentioned that acupuncture may help to overcome CLBP. However, since CLBP is a chronic condition, patients have to be realistic about treatment benefits. Only about half of the patients will benefit from acupuncture and professionals are unable to decide in advance if acupuncture will be beneficial for a specific patient. It will also be outlined and explained that sham acupuncture has a comparably high success rate. In the booster session, the medical doctor will do an assessment of back pain and limitations in daily life caused by back pain. The change of symptoms will be assessed: In case of worsening the patient will get the information that the patient might be a non-responder but he/she has to be patient. In case of an improvement the patient does not get any specific affirmation of progress but the doctor will note this improvement in the patient documentation. In the written material, the focus will be on pain perception and limitations. In contrast to the positive message (see above), the patient will be encouraged to focus on situations where pain is still present. The patient should describe situations according to the when?, what happened?, what did you do? matrix.

### **8.2.4 Control Intervention B) Side Effects**

A *regular briefing about side effects* is part of the informed consent and will be delivered to all four groups. The regular safety briefing means that no additional information about side effects will be provided in the briefing sessions.

## **8.3 Compliance with Intervention**

Regular appearance of patients to the acupuncture sessions is an indicator of compliance. Moreover, we will assess compliance of the briefing intervention and the acupuncture by reports of the professionals.

## **8.4 Data Collection and Follow-up for Withdrawn Participants**

We will assess possible reasons for withdrawal or dropout at the last visit before dropout. A follow-up of withdrawn patients is not intended.

## **8.5 Concomitant Intervention(s)**

Patients will be allowed to use oral non-steroidal anti-inflammatory drugs, if required (rescue medication). The use of corticosteroids or pain-relieving drugs that act through the central

nervous system, however, will be prohibited (specified list is in a studyspecific SOP). Any concomitant pain medication will be documented in the weekly diary (see document P6).

## 9 STUDY PROCEDURES

### 9.1 Study Flow Chart/Table of Study Procedures and Assessments

[figure not shown]

### 9.2 Assessments of Outcomes

#### 9.2.1 Assessment of Primary Outcome

Patient expectations of acupuncture treatment (EAT) will be assessed by a self-report questionnaire. The main outcome measurement takes place at baseline, after the first face-to-face briefing intervention and after 2 weeks of treatment.

The back pain severity will be assessed by a numeric rating scale NRS asking for the average pain severity in the last 7 days (0-10) after 4 weeks of treatment.

For the side effects we will use a score that summarizes the side effects after the total duration of the treatment at 4 weeks: Before each acupuncture treatment session, side effects of the last treatment will be assessed and for each reported side effect patients will be asked to rate the intensity on a scale from 1-3 (low, moderate, strong). All intensity numbers will be summarized in the side effect score.

#### 9.2.2 Assessment of Secondary Outcomes

Back pain severity: assessed as a secondary outcome by a numeric rating scale NRS (0-10) at 2 weeks (short term impact).

The back pain bothersomeness will be assessed by a numeric rating scale NRS asking for the average back pain bothersomeness in the last 7 days (0-10).

Self-reported health: PROMIS 29 (Patient-Reported Outcomes Measurement Information System) (Cella et al., 2010; Fries et al., 2011; Liu et al., 2010; Rothrock et al., 2010) is a well validated measure that was developed from the National Institutes of Health (NIH) in the USA

and is also available also in German. The PROMIS 29 is suggested as standard measure for CLBP studies by NIH (Deyo et al., 2014). Its profile covers the dimensions of anxiety, depression, fatigue, pain interference, physical function, sleep disturbance, and ability to participate in social roles and activities. All domains encompass four items with the exception of pain, which is measured by a single item. It will be measured at baseline, after 2 and 4 weeks of acupuncture and at the 6 months follow-up.

Working alliance with the acupuncturist: We will use 4 items of the Working Alliance Inventory (WAI-SR), (Wilmers et al., 2008) which measure the outcome on a 5 point scale. It will be measured after the first and the last acupuncture session.

We use the Perceived Sensitivity to Medicines Questionnaire (PSM), (Horne et al., 2013) to assess the belief to be influenced by medicines and experience side effects. It will be measured with 5 items on a 5 point Likert scale at baseline and at the end of the study.

Pain rescue medication (Brinkhaus et al., 2006): We will use a weekly diary to document the use of pain continuously. Patients will receive each week a new week-diary.

### **9.2.3 Additional measures:**

We measure the optimism with the Life-orientation Test (LOT-R), (Glaesmer et al., 2008) at baseline.

Empathy of the physician: We will measure empathy using the German Version of the "Consultation and Relational Empathy" (CARE) instrument (Neumann et al., 2008). The CARE is a one dimensional measure that consists of 9 items with a 5 point Likert scale. We will ask patients to complete it after the briefing and before the first acupuncture session.

Post-treatment guess: After completion of treatment, acupuncture therapists will be asked to guess which interventions patients received and their confidence with this guess. This will allow checking whether treatment providers were successfully blinded to briefing assignments.

Patients will be also asked to guess which briefing interventions they received. The patient guesses will be obtained after disclosure of the study aim at the end of the study (see ethical considerations), which might inform us about the success of the experimental manipulation.

## **9.2.4 Assessment of Safety Outcomes**

### **9.2.4.1 Adverse Effects**

We will measure adverse effects (= side effects of acupuncture treatment). See primary outcome (hypothesis 2).

### **9.2.4.2 Serious Adverse Events**

Patients will be asked about serious adverse events by the acupuncturists (see documents A1 and A2). Moreover, patients will be advised to inform the study office if any serious unexpected event occurs. We will document this in the SAE report form.

### **9.2.5 Assessments in Participants who Prematurely Stop the Study**

We will assess the causes for dropout by a questionnaire (document P11). We do not intend to have a follow-up of withdrawn patients.

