### 4.2 Adherence and Protocol Deviations

A few patients did not fill in the baseline questionnaire. Baseline values are, therefore, missing. A few patients stopped the acupuncture treatment prematurely and did not receive the foreseen eight acupuncture session. All patients received the briefing intervention as foreseen. Some patients used opioids between acupuncture sessions, which was initially an exclusion criteria at baseline if used on a regular basis.

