### 4.3 Analysis Population

- For research question 1a, there are very few patients who did not fill in the baseline questionnaire. An intention-to-treat analysis will be performed using multiple imputation (cf. Section 6.5) to handle missing values.
- For research questions 1b, an intention-to-treat analysis will be performed using multiple imputation (cf. Section 6.5) to handle missing values.
- For research questions 2, an intention-to-treat analysis will be performed (no missing data handling needed, cf. Section 6.2.3).
- In a sensitivity analysis (cf. Section 6.4.1), per-protocol analyses will be done using a complete-case data set (research questions 1a and 1b). In addition, to assess the influence of protocol deviations (cf. 6.4.2), the analyses will be repeated without patients that used opioids (for research question 1b), and only with patients that had at least 6 out of the 8 acupuncture treatment sessions (for research question 1b), respectively.

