## 6 Analysis

### 6.1 Outcome Definitions

The three primary outcomes are

- 1a) Expectation of acupuncture treatment (questionnaire "P2 EAT", now called ETS, but will be labelled with EAT in this SAP), a score based on 5 questions having each 4 levels. It can range from 5 to 20. The questionnaire is filled in by the patients at baseline before the treatment (*i. e.* the briefing by the study doctor), immediately after the treatment, and once more after the 4th acupuncture session (in week 2).
- 1b) Average pain intensity over the last 7 days after 4 weeks at the end of the treatment (questionnaire "P7.2 NRS"). As a measure, a numeric rating scale (NRS) is used in a self-reporting fashion. The NRS has 11 discrete levels from 0 (no pain) to 10 (worst pain possible). The NRS is filled in at baseline (before the treatment), after two weeks, and at the end of the acupuncture sessions. Note that due to eligibility criteria, only patients with an NRS value  $\geq 4$  were included in the study. Accordingly, the baseline values of pain intensity lie within the range of 4–10.
- 2) The side effects score after each acupuncture session (questionnaire "P9 Nebenwirkungen"). A self-report questionnaire with 13 questions and 4 levels each (0 to 3) is used, thus the values range from 0 to 39 per session. As a secondary outcome, the total side effect score for each patient, adjusted for the number of acupuncture sessions that the patient actually received, will be used.

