### **5 STUDY OUTCOMES**

#### **5.1 Primary Outcome**

We have two independent research questions (hypotheses 1 and 2) and overall three primary outcomes for these questions.

The primary effectiveness briefing outcome is the expectation of acupuncture treatment (EAT) of patients before their first acupuncture treatment (after the first face-to-face briefing intervention). Patient expectations will be assessed by a self-report measure using a Likert scale and a numeric rating scale. The final EAT score can range from 1 to 10.

A second primary outcome is back pain severity, which will be assessed by a numeric rating scale, measuring the average back pain intensity over the last 7 days after 4 weeks.

The primary safety briefing outcome is the side effect score. Side effects of the last treatment will be documented before each treatment (=adverse effects) and for each reported side effect patients will be asked to rate the intensity on a scale from 1-3 (low, moderate, strong). The intensity numbers will be summarized in a side effect score. We assess the side effects in order to measure the effect of the placebo briefing.

In the statistics section is described how the multiple primary endpoints are handled to rule out multiple testing.

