### **9.3.7 Visit 5-8**

Sessions 5 to 8 will be the final four acupuncture sessions, which take place within 2 weeks. Each time, side effects and rescue medication diary will be recorded or checked, respectively, before the acupuncture starts. After visit 6, the patients will again receive an email/letter booster as after visit 3. After the very last acupuncture session (visit 8), the acupuncturist will answer the post-treatment questionnaire (A3) and the patient will fill in the acupuncturist's alliance questionnaire (WAI-SR, P5). Moreover, pain (P7), PROMIS (P3) and PSM (P8) will be assessed.

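### Patients who stop acupuncture early have no scheduled 4-week pain score, so their part of primary outcome 1b rests on imputation under MAR; one page or call at week 4 would reduce this cheaply

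*Combined protocol and SAP*

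**What the plan says.** **Definition.** Protocol 5.1 defines the second primary outcome as a numeric rating scale "measuring the average back pain intensity over the last 7 days after 4 weeks". Protocol 9.2.1 repeats this: "asking for the average pain severity in the last 7 days (0-10) after 4 weeks of treatment". SAP 6.1 treats the calendar time and the end of treatment as one point: "Average pain intensity over the last 7 days after 4 weeks at the end of the treatment".

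**Collection.** The study schedule places pain form P7 at visits 4 and 8, and the next pain score is the month-6 questionnaire. Protocol 9.3.7 says of the time after the last session: "Moreover, pain (P7), PROMIS (P3) and PSM (P8) will be assessed". SAP 6.1 agrees: "The NRS is filled in at baseline (before the treatment), after two weeks, and at the end of the acupuncture sessions". The analysed variable in SAP 6.2.2 is nrs_8_1, whose time point in the SAP glossary is after session 8.

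**Early stopping.** Protocol 9.2.5 provides a dropout questionnaire (P11) on causes and then says "We do not intend to have a follow-up of withdrawn patients". Protocol 8.4 says the same. SAP 4.2 confirms that early stopping occurred: "A few patients stopped the acupuncture treatment prematurely and did not receive the foreseen eight acupuncture session". It gives no number.

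**Analysis.** SAP 4.3 states "For research questions 1b, an intention-to-treat analysis will be performed", with multiple imputation for missing values. SAP 6.5 assumes MAR.

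**The concern.** The randomised intervention is the briefing, not the acupuncture. The main briefing precedes session 1, the face-to-face booster comes at the second session, and SAP 4.2 reports that all patients received the briefing. Pain at week 4 is therefore a meaningful intention-to-treat outcome for a patient who later stops acupuncture. The plan ties its measurement to attending session 8.

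What puts a patient at risk of missing the score is stopping treatment, and stopping may be related to pain. If the share who stop, or how far their pain departs from what the model predicts, also differs between briefing arms, the 1b comparison is biased and the planned analyses would not show it. The protocol never distinguishes a patient who ends the sessions from one who leaves the study, so nothing directs staff to keep collecting data from the first kind.

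**Working it through.** **1. Is there any route to a 4-week score without session 8?** The schedule has no pain assessment between visit 8 and month 6. No procedure in Protocol 9.3 gives one to a patient who has stopped, and Protocol 8.4 and 9.2.5 exclude follow-up of withdrawn patients. So none is scheduled. This follows from the schedule, not from an explicit rule about patients who stop acupuncture only.

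**2. Does the analysis cover the gap?**
- The 1b imputation list in SAP 6.5 contains first-visit pain but not week-2 pain (nrs_4_1), although patients who stop after session 4 may have that score. By contrast, the month-6 imputation model in SAP 6.6.5 does include the preceding score, nrs_8_1.
- The sensitivity analyses in SAP 6.4 are complete cases, exclusion of opioid users, at least 6 of 8 sessions, and added covariates. Protocol 11.3.2 also mentions other imputation methods (hot deck, regression). None of these examines departure from MAR.

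**3. The plan's own figure for 1b.** Inputs from Protocol 11.2: SMD 0.38, two-sided 5%, n = 128 to 150, stated power 56–65%. With n patients per arm, power ≈ Φ(0.38·√(n/2) − 1.96).
- n = 64 per arm: Φ(2.150 − 1.96) = 57.5%; the t-test gives 56.9%.
- n = 75 per arm: Φ(2.327 − 1.96) = 64.3%; the t-test gives 63.8%.

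The stated range is reproduced. Its ends correspond to losing all planned dropouts (150 − 128 = 22) and losing none. Recovering every one would add at most 63.8 − 56.9 = 6.9 percentage points, and recovering half (n = 139) gives 60.4%. Power is the smaller part of the matter.

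**4. Illustrative bias.** Let p be the share with a missing score and δ the amount by which their true pain exceeds the imputed value. Each arm mean is understated by p·δ, so the estimated difference (high minus regular) is off by p_regular·δ_regular − p_high·δ_high. The documents give neither p by arm nor δ, so all values below are assumptions.
- 20% missing in the regular arm, 10% in the high arm, δ = 1 to 2 NRS points in both: (0.20 − 0.10) × 1 to 2 = 0.1 to 0.2 points.
- Planning effect on the NRS at an assumed SD of 2.0: 0.38 × 2.0 = 0.76 points.
- Ratio: 0.1/0.76 = 13% and 0.2/0.76 = 26%.
- 15% missing in both arms, δ differing by 0.5 SD between arms: 0.15 × 0.5 = 0.075 SD, or 20% of 0.38. Differing by 1 SD: 0.15 SD, or 39%.
- Equal p and equal δ in both arms: 0.

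**Direction.** If stoppers are worse than imputed and more of them are in the regular arm, regular-arm pain is understated and the briefing effect shrinks. If more are in the high arm, it is exaggerated by the same amount.

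**The case against.** The best defence is that early stoppers are not excluded: multiple imputation keeps them in the intention-to-treat set. SAP 4.2 speaks of only a few, whereas the 15% is a planning figure. SAP 5.5 already reports missing counts by randomised group, and SAP 6.5 reports the fraction of missing information. The last patient visit was on 11 December 2017 and the SAP is dated 29 May 2018, so nothing more can be collected at week 4. All of this stands. It limits the size of the problem and splits the remedy into a design part and an analysis part, but the missing values still depend on an assumption that the plan does not test.

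A reader might also infer more than the documents support:
- *That every patient with fewer than 8 sessions lacks the outcome.* SAP 6.1 refers to the end of the sessions, and the analysis of patients with at least 6 sessions leaves room for observed values in some of them.
- *That a pain item on P11 would supply the endpoint.* P11 is completed at the last visit before dropout (Protocol 8.4) or after it (schedule footnote). It would record pain around stopping, not at week 4.
- *That the date of session 8 drifts widely.* The 2–7 day interval is stated only for visits 2 and 3. Elsewhere the plan is two sessions a week over four weeks, with sessions 5–8 inside two weeks and dates confirmed beforehand. Chaining the interval across all visits goes beyond the text, and there is no need to redefine 1b around a day-28 window.
- *That the regular briefing drives patients out.* Protocol 8.2.3 tells a worsening patient that non-response is possible, but also asks for patience. A link between arm and stopping is possible; the documents do not show one.

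**Conclusion.** The point holds as a cheap improvement. Outcome 1b is defined at 4 weeks, but no 4-week score is scheduled for a patient who does not reach session 8, and data collection after stopping acupuncture is not provided for. For such patients without an observed end-of-treatment value, the intention-to-treat result rests on MAR, with an available predictor left out and no check on departures.

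The actual size is unknown because the number of stoppers, their arms and their pain are not given. Under the assumed 20% versus 10% split and a 1–2 point excess, the bias is 13–26% of the planning effect at an SD of 2.0. It is near zero when missingness and shift match across arms, and smaller than illustrated if few patients are affected. No power figure in the protocol is wrong.

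**What to change.** **Design (this protocol as a template for later trials).** Reword Protocol 8.4 and 9.2.5 so that stopping acupuncture does not end data collection. Collect the P7 7-day pain rating by mail or phone at the planned 4-week date from every randomised patient who has not withdrawn consent, however many sessions were attended.

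Cost: one page or call per stopper, at most about 22 patients at the planned dropout rate. The trial already mails the baseline and month-6 questionnaires. Some stoppers will not answer, and those who withdraw consent cannot be approached.

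**This trial (SAP amendment, made while the analysts are still blind to allocation).**
- Add week-2 pain (nrs_4_1) to the 1b imputation predictors in SAP 6.5.
- Add to SAP 6.4 a delta-adjusted sensitivity analysis that shifts imputed 1b values separately by effectiveness arm, for example by 0, 1 and 2 NRS points. State at which combinations the conclusion changes.
- Beyond the missing counts in SAP 5.5, report per arm how many 1b values are imputed because session 8 was not reached.

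Cost: a few extra model runs and one table, with no new data.
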